## Assessments

### Specification of efficacy parameters

#### Auxological parameters

The following growth parameters have been found to be meaningful to assess the efficacy of any treatment of patients with growth failure:Height Velocity (HV, cm/year) and HV Standard Deviation Score (HV SDS).Height Standard Deviation Score (H SDS).

Measurements of height should be preferably done with a stadiometer with 0.1 cm accuracy.

### Growth hormone parameters IGF-I and IGFBP-3

All IGF-I and IGFBP-3 values should preferentially be expressed as standard deviation score for age and the analytical method should be specified.

### BMI and body composition

Children: An improvement of body mass index (BMI) compared to baseline is expected.

Body composition (total fat mass, lean body mass, total body water) may be measured by e.g., Bioelectronical Impedance Analysis (BIA) or Dual Energy X-ray Absorptiometry (DXA) as assessed in clinical routine.

### Patient related outcomes

Patient related outcomes (PRO) capture a person’s perception of their own health through questionnaires.

PRO scales such as the Short Form 12 and others will be administered, either in a longitudinal design or at a given point of time in selected groups in a cross-sectional analysis.

### Short form 12 (in patients aged 14 years and over)

The SF-12 is a health-related QoL questionnaire consists of a subset of twelve questions, derived from the Short Form 36 (SF-36) questionnaire, that measures eight health domains to assess physical and mental health [11]. Physical health-related domains include General Health, Physical Functioning, Role Physical, and Body Pain. Mental health-related scales include Vitality, Social Functioning, Role Emotional, and Mental Health [12].

The self-administered version of SF-12 will be used. A physical component score (PCS) and mental component score (MCS) can be calculated. Country-specific weights are available for various countries including Germany.

### Safety assessments

Safety assessments will consist of all adverse events (overall, and all causally related and/or temporally associated AEs).

### Data collection and quality control

The Sponsor is responsible for implementing and maintaining a quality management system with written development procedures and functional area standard operating procedures (SOPs) to ensure that studies are conducted and data are generated, documented, and reported in compliance with the protocol, accepted standards of Good Epidemiological Practice (GEP) [13], and all applicable laws, rules and regulations relating to the conduct of the registry [14].

Before registry start at the sites, all investigators are sufficiently trained on the background and objectives of the study and ethical as well as regulatory obligations.

Data are collected by the centres online, using a secure connection (no paper–pencil CRFs are be used). The electronic data capture system (EDC) with electronic data collection forms (eCRFs) and other features (e.g., repository of registry documents) is provided by GWT-TUD. No software applications need to be installed by the sites. The web-based EDC application is password protected. User account requests are authorized by GWT-TUD. A manual with instructions how to use the EDC has been made available to sites.

The data are entered by the investigator or registry site personnel via a secure internet connection into the registry database. Only these persons can record or change data relating to patients in their centre on the CRFs.

Detailed information on checks for completeness, accuracy, plausibility and validity are given in the Data Management Plan (DMP). The same plan specifies measures for handling of missing data and permissible clarifications.

Upon entry, the data is automatically checked for completeness and plausibility.

As part of the statistical processing, the data is checked again and queries are sent to the centre if necessary. If needed, requests are sent to the sites to correct incorrect inaccurate data or complete missing data.

In about 10% of the centres, an audit will be carried out to check the correct data entry while respecting data protection (monitoring with comparison of the registry data with original patient data).

## Statistical analysis

### Sample size

As the present registry has mainly descriptive aims, there is no formal power calculation needed to determine the target sample size [15]. Rather, the sample size is determined by feasibility aspects.

Based on outcomes of a recent international registry-type observational study with a cohort of 83.803 patients, it is expected that 56.9% of patients will have different causes of GH deficiency, 9.5% small for gestational age (SGA), 9.2% Turner syndrome, 2.8% Prader–Willi-syndrome, 2.9% chronic renal insufficiency and 18.7% will have other conditions treated with GHT [16].

From a drug safety perspective, an enrolled number of 1500 patients according to the “rule of three” will allow for the detection of AE occurring at an incidence of 1/500 person-years [17, 18]. If the median observation duration is 2.5 years, an AE occurring with an incidence of 1/1250 person-years will be detected.

### Descriptive analysis and statistical testing

Data will be analysed in regular (e.g., six months) intervals. This will be done to keep sites appraised of the progress of the registry and to review data quality (rate of missing values; data distribution, outliers).

All background variables and outcome parameters will be analysed descriptively with appropriate statistical methods: categorical variables by frequency tables (absolute and relative frequencies) and continuous variables by summary statistics (i.e., mean, standard deviation, minimum, median, quartiles and maximum). Continuous variables will also be described by absolute value and as change from baseline per analysis time point, if applicable.

Analyses will be performed for the total study population (overall analysis) and separately by indication or relevant subgroups (e.g., age, sex, GH pretreated and treatment-naive patients), if patient numbers are sufficient. Pretreated patients are here defined as patients already on treatment when enrolled in the study, whereas treatment-naive patients will be patients newly starting GHT.

The Statistical Analysis Plan (SAP) will specify details of the analysis.

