## Methods

### Objectives and endpoints

The objectives and corresponding endpoints of the registry are shown in Table 1.

**Table 1 Tab1:** Objectives and endpoints

	**Objective**	**Endpoints**
**Primary**	To analyse somatropin drug utilization within routine clinical practice in a diverse population of children and adults, across all GH products To determine the place of long-acting GH in practice	Utilized GH preparations Dose and dosing schedule (daily vs. long-acting) Duration of treatment Persistence Switches between GH treatments Interruption/ discontinuation of GH treatment
**Secondary**	**Efficacy** To describe the long-term efficacy of somatropin To assess the transition from adolescence to adulthood	Paediatric indications: Real final adult height (using stadiometer) Adult indication: Body composition (all methods) Delta IGF-I standard deviation score (SDS, change during treatment / normalization) Delta height standard deviation score (SDS) / delta lean body mass Body proportions (sitting height; standing height), Delta target height vs height SDS Lipid status, inflammation markers, IGF-I, blood pressure Analyses stratified according to different diagnosis groups
	Persistence	Persistence calculated as duration of time from initiation to discontinuation of therapy
	Patient related outcomes (PRO) To describe patient PRO, including quality of life and patient experience over the initial 2 years of GH treatment, cross-sectional and long term (children and adults)	Satisfaction with treatment experience Quality of life, e.g., by SF-12 (in adults and adolescents) Additional validated self-reported or observed (e.g., parent- or partner-rated) QoL and PRO questionnaires can optionally be used
	**Safety** To describe the long-term safety of somatropin	Number and rate per patient-years of Adverse events All causally related and/or temporally associated AEs
**Exploratory**	Exploratory: To assess / analyse additional parameters potentially modulated by GHT To assess subgroups of the population under observation, or to assess outcomes by participating centres	e.g., body composition by DXA

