### Subject completion

Subject may be followed up in the registry until the final registry termination. There is a planned minimum follow-up period of 3 years, but no maximum follow-up period. Interruptions of GHT are acceptable, and in such cases the patient can remain in the registry. Switches from one to another GH preparation does not qualify as subject completion, i.e., patients can remain in the registry.

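### The persistence definition and the stated summary statistics together give no valid handling of patients still on growth hormone

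*Protocol article*

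**What the plan says.** In Table 1 (Objectives and endpoints) the primary objective is "To analyse somatropin drug utilization within routine clinical practice in a diverse population of children and adults, across all GH products". The endpoints beside it include duration of treatment, persistence, interruption or discontinuation, and "Switches between GH treatments". Persistence appears again in a secondary row, which holds its only definition: "Persistence calculated as duration of time from initiation to discontinuation of therapy".

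The section Descriptive analysis and statistical testing covers every endpoint: "All background variables and outcome parameters will be analysed descriptively with appropriate statistical methods". It then names the methods: "categorical variables by frequency tables (absolute and relative frequencies"), and "continuous variables by summary statistics (i.e., mean, standard deviation, minimum, median, quartiles and maximum"). It leaves the details to the statistical analysis plan (SAP), and the Coding section leaves calculated variables to it as well.

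On follow-up, Subject completion states: "There is a planned minimum follow-up period of 3 years, but no maximum follow-up period". The Conclusion gives a field phase from February 2022 to at least December 2024. The abstract admits patients on ongoing as well as newly started treatment.

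Subject discontinuation lists the reasons for stopping growth hormone treatment (GHT). Beside end of GHT it names withdrawal of consent, a move to a non-participating centre and loss to follow-up.

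**The concern.** Time from start to stop exists only for patients who have stopped. In an open cohort with staggered entry, and with children expected to be treated until final height, many patients will not have stopped at any data cut. Mean, standard deviation, median and quartiles can then be computed in only two ways: leave those patients out, or use their time so far as if it were complete. Both make persistence look shorter than it is, and both depend mainly on how long the registry has run. Crude percentages discontinued have a related weakness, because they mix patients with a few months of observation and patients with nearly three years.

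The list of reasons under Subject discontinuation makes this worse. Withdrawal of consent, change of centre and loss to follow-up end the observation, not the therapy. Coded as the list reads, a patient who moves centre while still on treatment becomes a completed duration.

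The article does use an exposure denominator elsewhere: the safety row of Table 1 asks for "Number and rate per patient-years of" adverse events. The primary utilisation endpoints have no counterpart.

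**Working it through.** **The plan's own figure.** The article gives no figure for persistence. Its only computed figure is the rule of three for safety, and it reproduces: 1500 / 3 = 500 and 1500 × 2.5 / 3 = 1250. The present point does not depend on it.

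**Inputs from the article.** Field start February 2022 (taken as 1 February); 770 patients by 8 May 2023; target 1500; field phase to at least December 2024 (taken as 31 December).

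**Assumptions.** Uniform accrual at the observed pace; all patients start GHT at enrolment; constant stopping rate h of 5%, 10%, 20% or 30% per year. The article states no stopping rate.

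**Step 1: follow-up.**
- Accrual period: a = (461 days × 1500 / 770) / 365.25 = 2.459 years.
- Longest follow-up: T = 1064 / 365.25 = 2.913 years.
- Shortest follow-up: L = 2.913 − 2.459 = 0.454 years.
- Mean follow-up: (2.913 + 0.454) / 2 = 1.68 years.

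So no patient reaches three years by December 2024 unless the field phase runs longer.

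**Step 2: share still on treatment at the cut.** With follow-up uniform on (L, T), the share is [exp(−hL) − exp(−hT)] / (h·a). At h = 0.10 this is (0.9556 − 0.7473) / 0.2459 = 0.847, so the crude share discontinued is 15.3%.

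**Step 3: medians.** The true median is ln 2 / h; at h = 0.10 it is 0.693 / 0.10 = 6.93 years. The two literal summaries and the Kaplan-Meier estimate come from a simulation of 1,000,000 new starters. A direct calculation from the same distributions gives the same medians.

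| Stopping rate per year | Still on GHT at cut | True median (years) | Median, stopped only (years) | Median, all durations cut (years) | Kaplan-Meier 2-year persistence | True 2-year persistence |
|---|---|---|---|---|---|---|
| 5% | 92% | 13.9 | 0.85 | 1.58 | 0.904 | 0.905 |
| 10% | 85% | 6.9 | 0.82 | 1.49 | 0.819 | 0.819 |
| 20% | 72% | 3.5 | 0.77 | 1.31 | 0.671 | 0.670 |
| 30% | 62% | 2.3 | 0.72 | 1.17 | 0.549 | 0.549 |

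A sixfold change in the stopping rate moves the stopped-only median from 0.85 to 0.72 years. Kaplan-Meier recovers the true 2-year figure to within 0.001.

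**Step 4: pretreated patients.** Persistence counts from initiation, but pretreated patients come under observation only at enrolment and are there because they had not stopped. Assume starts spread evenly over 0 to 10 years before enrolment.

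| Stopping rate per year | True 5-year persistence | Kaplan-Meier ignoring late entry | Kaplan-Meier with delayed entry |
|---|---|---|---|
| 10% | 0.61 | 0.90 | 0.61 |
| 20% | 0.37 | 0.77 | 0.37 |

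A plain Kaplan-Meier curve from initiation would therefore err in the opposite direction for this group.

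**The case against.** The strongest reply is that the article fixes less than it seems to. It promises appropriate methods and leaves details and calculated variables to a SAP that is not shown. Kaplan-Meier and cumulative incidence are themselves descriptive and would fit. This stands, and it limits the conclusion. A reader might infer that patients still on treatment will be dropped or counted as finished. No passage says so, and the sections on interruption and on subject discontinuation say that data up to the end of participation are used. The deferral does not remove the point altogether: the text assigns all outcome parameters to two kinds of summary, introduces the continuous list with i.e. rather than e.g., and pairs it with a definition that has no value for a continuing patient.

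Three further objections stand:
- Switches and interruptions can recur and are not defined as times, so counts are a legitimate description of them. To call every utilisation endpoint a time-to-event outcome would go too far.
- A reader might infer that misleading percentages would be reported every six months. The article gives those analyses the purpose of informing sites and reviewing data quality, not of estimating persistence.
- The sizes rest on assumed rates. A constant rate is a rough fit where children are treated until final height, and the field phase may run past December 2024. The contrast for crude discontinuation is also modest: at 10% per year, 15.3% at a mean follow-up of 1.68 years against a true 18.1% (1 − 0.819) at two years.

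**Conclusion.** The point holds as a defect in the stated text: the definition in Table 1 and the list in the analysis section together provide no valid way to summarise persistence or discontinuation for patients still on treatment. The list of discontinuation reasons adds to this by mixing ends of observation with ends of therapy. With assumed stopping rates of 5% to 30% per year, uniform accrual, new starters only and a December 2024 cut, about 62% to 92% would still be on treatment. A literal reading would report a median of 0.7 to 0.9 or 1.2 to 1.6 years in place of 2.3 to 13.9 years. The direction and rough size are robust over that range; the exact values are illustrative. Whether the registry's reports would carry this error cannot be settled from the article, because the SAP may already specify a method that handles censoring.

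**What to change.** In the analysis section and Table 1, and in the SAP:

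- Describe persistence and discontinuation by Kaplan-Meier or cumulative incidence with 95% confidence intervals, at fixed times that follow-up supports: for example 12 and 24 months, and 36 months only if documentation runs beyond December 2024.
- Censor patients still on GHT at their last documentation. Treat withdrawal of consent, change of centre, loss to follow-up and administrative ends as censoring, and reconcile the list under Subject discontinuation so that end of therapy and end of observation are recorded as different things.
- Report treatment-naive patients separately from pretreated patients, or use delayed entry at enrolment for the pretreated.
- Report switches and interruptions as rates per patient-year of observed treatment, beside the counts. Frequency tables remain suitable for the preparations used.

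The cost is a change of wording and a little more analysis. Start and stop dates of treatment are already collected at the inclusion and follow-up visits, so no new data are needed. If the SAP already contains these rules, it is enough to align the article's wording with it.

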### Coding

Concomitant medication will be coded using the WHO Drug Dictionary and tabulated by ATC term. Medical history, diseases and AEs will be coded by MedDRA in its current version [19], and/or by International Classification of Diseases (ICD).

All statistical details including calculated variables and proposed format and content of tables will be detailed in the SAP, which will be finalized before study database lock.

### Dissemination and communication of results

The information obtained during the conduct of this registry is considered confidential.

However, it is the explicit aim to publish the design, methods, results and insights derived from the registry.

The results of this registry are intended to be published in a series of articles in peer-reviewed journals and as abstracts/presentations at medical congresses under the oversight of the sponsor. Current guidelines and recommendation on good publication practice will be followed (e.g. STROBE [20]). No individual investigator may publish on the results of this study, or their own patients, without prior approval from the sponsor.

The site physicians will not disseminate any publication or release pertaining to the registry and/or results of the registry without consultation of the Sponsor and the Steering committee. Different parts of the registry may be published separately.

## Results

At the present time, there are no results available.

## Discussion

The INSIGHTS-GHT registry aims to document at least 1500 patients who receive treatment with GH. It has been designed to further the clinical understanding of this various indications that require the administration of GH, in a broad patient population across all age groups. The end goal of this registry is the synthesis, publication and dissemination of real-world evidence from the collected data, which can be used to improve both the understanding and clinical management of conditions that require GH. No other national registry on GH preparations is ongoing in Germany.

The registry documents children and adults in one joint registry, includes, at present, patients in Germany and allows documentation of patients on all approved somatropin and other growth hormone preparations. Once available, also the new long-acting GH preparations will be documented. Of note, INSIGHTS-GHT will allow to describe the transition of patients from adolescence to adulthood (with focus on treatment and final height), to describe switches between somatotropin preparations, to perform responder analyses, and to analyse differences and similarities of somatropin utilization (by age group, sex, setting, and PRO instrument).

A fundamental limitation of the INSIGHTS-GHT registry could be due to the different institutions involved in the registry and their recording of the collected auxological, laboratory chemistry, and radiological routine monitoring data. Because the registry is not a clinical trial, there is no mandatory data set to be collected other than informed consent and demographic data. To mitigate this limitation, the Steering Committee has created a core data set based on existing disease guidelines that would be desirable to use. This core data set will help standardize information across all institutions participating in the registry. In addition, we consider the limited applicability of the FAIR principles (discoverability, accessibility, interoperability, and Reuse of Digital Resources) [21] in their entirety to this clinical trial of GH use in the various approved indications as a potential limitation. This is due to existing privacy and confidentiality restrictions on the use and sharing of patient-level data. Although the patient-level data will not be publicly available, the results of aggregate data from the INSIGHTS-GHT Registry will be published in peer-reviewed journals. In addition, because the INSIGHTS-GHT Registry is registered under the BfArM No. NIS7492 and DRKS Registry DRKS00027394, the information is publicly available and appropriately qualified individuals may request access to the registry for research purposes.

## Conclusion

The study was initiated by investigators (see authors). The legal sponsor is the GWT-TUD GmbH in Dresden. The study entered the field phase in February 2022, and has enrolled 770 patients to date (08 May 2023). The field (documentation) phase of the study is planned until (at least) December 2024. The study is progressing as planned. So far, 23 centres are contributing patient data and the number is steadily increasing. The good progress is remarkable because there are currently several new PASS studies documenting long-acting preparations, so there are competing study projects in the centres.

## ICD and ORPHANET codes of diseases

**Table Taba:** 

Disease	ICD-10	ORPHANET codes
Growth hormone deficiency (GHD)	E23.0	631, 91354, 467, 90695
		231662, 231671, 231679, 231692
Ullrich-Turner syndrome	Q96.0–96.9	881
Noonan syndrome	Q87.1	648
Prader–Willi syndrome	Q87.1	739
SHOX deficiency	Q87.1	not avaible (no rare disease)
Chronic renal failure	N17-N19	not avaible (no rare disease)

Patients with other conditions treated with GH are eligible for documentation

## Data Availability

Data sharing is not applicable to this article as datasets are being generated but have not been analysed during the current study.

## Abbreviations

AE: Adverse event
ATC: Anatomical therapeutic chemical (classification system)
BfArM: Bundesinstitut für Arzneimittel und Medizinprodukte
BIA: Bioelectronical impedance analysis
BMI: Body mass index
CRF/eCRF: Case report form/electronic case report form
CRI: Chronic renal insufficiency
DXA: Dual-energy X-ray absorptiometry
EDC: Electronic data capture
GH: Growth hormone
GHD: Growth hormone deficiency
GHT: Growth hormone treatment
HDL: High density lipoprotein
HV: Height velocity
IGF-I: Insulin-like growth factor 1
IGFBP-3: Insulin-like growth factor-binding protein 3
IHT: Insulin hypoglycemia test
INN: International nonproprietary name
LDL: Low density lipoprotein
MedDRA: Medical dictionary for regulatory activities
PWS: Prader-Willi syndrome
QoL: Quality of life
SAP: Statistical analysis plan
SDS: Standard deviation score
SF-12: Short form 12
SGA: Short for gestational age
SmPC: Summary of product characteristics
WHO: World Health Organization
